#### Sham—Deactivated negative ion generator

The sham intervention consisted of a no-light, negative ion generator (SphereOne, Inc.) of comparable size and electricity demands to the LightPad, also shipped to participants at the end of their baseline period. All negative ion generator devices were modified to emit an audible quiet hum with a green status light, and deactivated to not emit ions, as previously published [28], which falsely indicated being in an active state. The sham arm followed identical timing and duration as described above for the active-MBLT arm. Therefore, participants in the sham arm also received the same degree of subject-investigator interaction and instructions for device adherence.

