#### Self-report, actigraphy, and sleep diary

Potential changes in sleep were further evaluated via other validated self-report measures (e.g., Epworth Sleepiness Scale, ESS [56]; Functional Outcomes of Sleep Questionnaire-10, FOSQ-10 [57]; and the Sleep Hygiene Index, SHI [58]), and objective metrics derived from participants’ sleep diary and wrist-based actigraphy (Philips Respironics, Bend, OR, USA). Philips Actigraphy devices use a solid-state, piezoelectric, monoaxial accelerometer to measure activity and silicon photodiodes to measure photopic light (5–100,000 lux; 400–900 nm), with data sampled at 32 Hz and aggregated into 2-minute bins. Philips Actiware (v 6.3.0) was used to process and analyze these data relying first on the automated algorithmic detection of rest-active periods, with further refinement based on *a priori* defined outcomes collected in the sleep diary. For example, participants were queried whether their sleep was unusually disrupted (ranging from being ill to falling asleep or being awoken at unusual times due to things outside of their control), and if so, this 24-hour period was excluded from analysis. Participants were directed to wear the watch on their non-dominant wrist and to keep clothing from covering the light sensor as much as possible. Daily sleep diaries were collected using the TWILIO^™^ platform, which directly integrated with our HIPAA-compliant secure REDCap database. Participants were prompted in the morning via Short Message Service (SMS) text format. The first prompt was at 8:00 AM in participants local time, with reminders sent at 10:00 AM and 12:00 PM if no response had been entered. If participants did not respond within that 24-hour period, earlier prompts expired ensuring all data is collected within 24 hours. Sleep diary metrics included self-reported time in bed/asleep, time out of bed/awake, number of awakenings during the night, and (during the intervention period) device usage.

The primary comparison across timepoints was pre- vs post-intervention. Only self-reported sleep symptoms were evaluated at the follow-up time point as daily diaries and actigraphy were not continued during the follow-up period.

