#### Secondary: Self-report

Additional relevant outcomes included a broad range of validated self-reported outcomes related to neurobehavioral function, mood, and quality of life (e.g., NIH PROMIS Global Health, Pain Intensity/Interference, and Emotional Distress Anxiety [59,60]; Neurobehavioral Symptom Inventory, NSI [61]; Post-traumatic Stress Disorder Checklist for DSM-5, PCL-5 [62]; Patient Health Questionniare-9, PHQ-9 [63]; World Health Organization Disability Schedule 2.0, WHO-DAS 2.0 [64]; and Sleep Hygiene Index, SHI [58]). On average, this questionnaire battery required 30–45 minutes to complete. Questionnaires were completed using REDCap, with all entries automatically recorded. If participants were unable to complete questionnaires electronically, these were printed, mailed and all entries manually recorded into REDCap with a secondary rater confirming data entry accuracy.

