### Statistical analyses

The statistical analysis plan was designed to be carried out using GraphPad Prism v9 or R, with alpha defined *a priori* at 0.05, using a thorough descriptive analysis of participant baseline characteristics prior to evaluation of outcomes. Categorical variables will be described using frequencies and percentages. Histograms and boxplots will be used to assess the distribution of continuous variables. Continuous variables that follow an approximately normal distribution will be summarized using means and standard deviations; skewed continuous variables will be reported as medians and interquartile ranges. Potential covariates will also be summarized with descriptive statistics and graphs. As part of our descriptive analyses, we will compare participants who complete versus drop out of the study by baseline characteristics and study arm to ascertain potential biases that may impact this and future studies. Effect size estimates will be reported as Cohen’s d (small = 0.2; medium = 0.5; large = 0.8) or standardized regression coefficients (β) (small = 0.14; medium = 0.39; large = 0.59). We will also report the number needed to treat (NNT) approximated using methods described by Kraemer and Kupfer [71]. The Benjamini-Hochberg procedure will be used to control the false discovery rate for primary outcomes. Statistical outliers will be identified using regression diagnostics to estimate Cook’s Distance, and then a cutoff of 4/n (n = number of participants) will be used to identify outliers. Outliers will be examined for data entry errors, but otherwise retained in analyses. If data violate parametric assumptions via Shapiro-Wilk test, test statistics will be derived using robust standard errors. We will use the intent-to-treat principle and include all participants randomized to treatment irrespective of treatment compliance.

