To analyze treatment effect over time (pre-, post-, and follow-up), we will implement mixed effects models (either linear or gamma, pending data normality) for each outcome measure under consideration. This flexible approach allows us to examine the change pattern and accounts for within-subject correlations over multiple time points. This approach also maximizes our observed data by way of accommodating missing data at random. The main effects in each model will be the treatment and time effects, including a treatment-by-time interaction effect. The models may be adjusted for possible confounders, such as age, sex, fidelity adherence (lux/min), geographic location/seasonality, sleep hygiene, and depression. With a significant omnibus test suggesting the global null hypothesis is rejected, a Bonferroni or Tukey HSD post-hoc analysis will be performed.

Within the MBLT group we will use linear regression to analyze the relationship (goodness of fit; r^2^) between average morning lux exposure (quantified as lux/min by the Actiwatch) and the degree of change in dependent variables (e.g., sleep efficiency, self-reported sleep quality, neurocognitive outcomes, and other self-reported functional outcomes) between pre- and post-treatment. Within select patient outcome questionnaires, we will perform Pearson correlational analyses to determine how each patient outcome questionnaire varies together (Pearson correlation coefficient; r). Actigraphy variables will be compared to appropriate self-report and objective outcomes in the form of discrete time-period averages (i.e., 3–5 consecutive representative nights within the last ~7 days of both the baseline and intervention periods). Secondarily, if permissible, we will implement analyses based on a 3-day moving average, leveraging the unique frequency of data acquisition inherent to 24/7 actigraphy.

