In establishing protocol acceptability, we first considered the rate of missing data and other errors present in major outcome assessments, within the 14-day baseline period. This was examined via participant response rates for sleep diary entries and actigraphy usage (Fig 4A and 4B). Response rates for daily sleep diary entries did not differ between the active (97%) and sham (86%) conditions (*p*>0.05). Similarly, the number of days participants provided usable actigraphy data did not differ between the active (91%) and sham (89%) conditions (*p*>0.05). Protocol acceptability specific to the intervention examined overall fidelity adherence, which has averaged 83–93% across study arms. No differences were detected in the rates of participants meeting threshold for fidelity adherence across study arms when referencing either self-report or the objective assessment (*p*>0.05). Noting that there was not an objective assessment of device adherence to the sham condition. This protocol’s *a priori* definition of “fully adherent” was that participants engage with the device on at least 70% of the intervention period (5 out of every 7 days; therefore, a minimum total of 20 out of 28 days). Accordingly, device adherence has on average exceeded expectations with most adherent participants reporting device use for >23/28 days (Fig 5A and 5B).

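### Fidelity adherence in lux/min is listed as a possible confounder for the between-arm models, but it is the delivered light dose, measured after randomisation

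*Protocol article*

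**What the plan says.** Statistical analyses in the protocol article plans mixed effects models for each outcome over the pre-intervention, post-intervention and follow-up visits. On their terms it says: "The main effects in each model will be the treatment and time effects, including a treatment-by-time interaction effect". It then adds: "The models may be adjusted for possible confounders, such as age, sex, fidelity adherence (lux/min), geographic location/seasonality, sleep hygiene, and depression". No covariate is limited to a baseline value.

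The same section plans a regression within the MBLT arm on "average morning lux exposure (quantified as lux/min by the Actiwatch"). That shows what lux/min is: measured morning light during the intervention.

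The sham section says: "The sham intervention consisted of a no-light, negative ion generator". On adherence, Results says: "Noting that there was not an objective assessment of device adherence to the sham condition".

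Sleep hygiene appears among the further sleep measures ("and the Sleep Hygiene Index, SHI [58"]) and again under Secondary: Self-report. Depression is measured there too ("Patient Health Questionniare-9, PHQ-9 [63"]).

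**The concern.** A confounder is a common cause of treatment and outcome. Randomisation removes such causes of arm, and a variable that the arm itself changes cannot be one. Light exposure during the intervention is a consequence of assignment and is the route by which MBLT is meant to work. Holding it equal across arms asks what MBLT does beyond the light it delivers, which is not the trial's question.

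Two harms follow. The part of the effect carried by light moves from the arm coefficient to the light coefficient. Also, because light nearly identifies the arm, the two are collinear and the standard error of the arm effect grows even if light carries none of the effect.

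SHI and PHQ-9 raise a milder form of the same problem. Their baseline values are legitimate covariates. Their post-intervention values may themselves respond to treatment, and the text does not say which are meant.

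The primary outcome (ISI) goes through these models, so the permission leaves open several different answers to the main question.

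**Working it through.** **Inputs from the protocol article.** 80 MBLT and 40 sham; between-group difference 7 (percentage points); SD 12 in MBLT and 7.3 in sham; two-sided alpha 0.05; stated power 85%.

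**Assumptions not in the article.** Light is scaled to mean 1, SD 0.35 in MBLT. Sham light is near 0 in the change-score check, and mean 0.2 (SD 0.1) in the mixed-model check. The share of the effect carried by light is varied from 0 to 100%.

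**1. Unadjusted starting point.** SE = √(12²/80 + 7.3²/40) = √(1.800 + 1.332) = 1.770. Power = Φ(7/1.770 − 1.96) = Φ(1.995) = 97.7%. The stated 85% is not reproduced from the two SDs. It appears only with SD 12 in both arms: SE = 12·√(1/80 + 1/40) = 2.324, power = Φ(7/2.324 − 1.96) = 85.4%. That is a separate matter and does not affect this point.

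**2. Change-score model with lux added.** With sham light near 0, the light slope is estimated almost wholly within MBLT. Its variance is about 12²/(80 × 0.35²) = 144/9.8 = 14.69. The adjusted arm effect is the raw difference minus slope × the light gap between arms (about 1). Its SE is therefore about √(1.770² + 14.69) = 4.22, and 4.22/1.770 = 2.4 times the unadjusted SE. Simulation (2,000 runs per setting) gave about 2.3-fold, and:

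| Share of effect through light | Adjusted arm effect | Power |
|---|---|---|
| 0% | 6.9 | 40% |
| 25% | 5.4 | 25% |
| 50% | 3.5 | 16% |
| 75% | 1.8 | 8% |
| 100% | −0.2 | 5% |

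Unadjusted power in the same runs was 96 to 98%. The first row is loss from collinearity alone.

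**3. Pre/post mixed model (random intercept, treatment-by-time, 2,000 runs).** Size of the treatment-by-time effect, with power in brackets:

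| Share through light | No lux | Lux constant over time | Lux by time | Lux time-varying |
|---|---|---|---|---|
| 0% | 7.1 (98%) | 7.1 (98%) | 7.1 (56%) | 7.0 (67%) |
| 50% | 7.0 (98%) | 7.0 (98%) | 3.6 (21%) | 3.9 (28%) |
| 100% | 6.9 (98%) | 6.9 (98%) | about 0 (6%) | 0.6 (7%) |

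The constant-lux column is unchanged because, in balanced data, a covariate that does not vary over time cannot explain change within a person.

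The treatment main effect (the arm difference at baseline, truly 0) is not spared. Under full mediation the light slope is 7/0.8 = 8.75 at post and 0 at pre, so a constant-lux term estimates the average, 4.375. Across a light gap of 0.8 this shifts the treatment main effect by 4.375 × 0.8 = 3.5 points. A rerun of the simulation gave 3.4.

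**4. PHQ-9 if post-baseline values were used.** Take the pooled SD of 10.7, r as the within-arm correlation of PHQ-9 with the outcome, and d as the treatment's shift in PHQ-9 in SD units. The remaining effect is 7 − r × 10.7 × d. With r = 0.3, d = 0.2 it is 6.36; with r = 0.5, d = 0.4 it is 4.86; with r = 0.6, d = 0.6 it is 3.15. Both r and d are assumed.

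**The case against.** The strongest reply is that the planned model is longitudinal and that the natural reading of lux/min is a single average per person. Actigraphy stopped before follow-up, so a time-varying value cannot cover all three time points. In that form treatment-by-time is unchanged, as step 3 shows. This stands, and it rules out saying that adjustment always removes the effect. It does not clear the covariate: the treatment main effect is still distorted, and the text does not fix the form of entry.

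The reply is also right that adjustment is optional, and that SHI and PHQ-9 do harm only as post-baseline values.

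Three stronger readings are tempting but unsupported:

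- A reader might infer that lux/min does not exist in sham. The Results remark concerns device adherence, and the separate light logger was fixed to the LightPad only. But sham participants also wore the Actiwatch, which records light; Table 3 gives averages of 24.9 and 23.8 actigraphy days for sham during the intervention. Sham lux exists; it measures ambient light.
- A reader might infer a breach of intent-to-treat. That commitment is to "include all participants randomized to treatment irrespective of treatment compliance", which governs who is analysed, and a covariate excludes nobody. The objection is to the question being answered.
- A reader might infer that the bias must be towards zero. Removing the mediated part does act that way when MBLT helps through light. However, unmeasured common causes of light exposure and outcome could push the adjusted estimate either way.

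**Conclusion.** The point holds as a wrong entry in the covariate list. Lux/min is a consequence of assignment and should not be offered as a confounder in any between-arm model.

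The size depends on how it enters. In a change-score model, by time, or as a time-varying term, the loss equals the share of effect carried by light: about half of 7 points at 50% mediation, and essentially all at 100%. The SE rises about 2.3-fold in the change-score case. As a constant main effect, treatment-by-time is untouched and only the treatment main effect is wrong. All these sizes rest on assumed light distributions and on pre/post data without follow-up. What does not depend on those figures is that the adjusted contrast is no longer the total effect of assignment.

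The documents do not show that the primary analysis will include lux/min, so a prediction that the trial will lose its effect would go too far. For SHI and PHQ-9 the need is only to state that baseline values are meant.

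**What to change.** In Statistical analyses:

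- Delete fidelity adherence (lux/min) from the covariates of the between-arm models.
- State that the remaining listed covariates (age, sex, location/season, SHI, PHQ-9) are values fixed before randomisation.
- Do not use baseline SHI or PHQ-9 as a covariate in the model where that same measure is the outcome, because its pre-intervention value is already one of the modelled time points. For the same reason, do not add pre-intervention ISI to the ISI model as specified.
- Keep lux/min for the dose-response regression already planned within MBLT, and label it a non-randomised comparison.

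The cost is a sentence or two of text. Table 3 shows the pre-intervention questionnaire battery complete in every group, so no new data are needed. Results states that the outcomes have not yet been formally analysed, so the change can still be made before any efficacy result is seen.

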## Abstract

Sleep-wake disturbances frequently present in Veterans with mild traumatic brain injury (mTBI). These TBI-related sleep impairments confer significant burden and commonly exacerbate other functional impairments. Therapies to improve sleep following mTBI are limited and studies in Veterans are even more scarce. In our previous pilot work, morning bright light therapy (MBLT) was found to be a feasible behavioral sleep intervention in Veterans with a history of mTBI; however, this was single-arm, open-label, and non-randomized, and therefore was not intended to establish efficacy. The present study, LION (light vs ion therapy) extends this preliminary work as a fully powered, sham-controlled, participant-masked randomized controlled trial (NCT03968874), implemented as fully remote within the VA (target n = 120 complete). Randomization at 2:1 allocation ratio to: 1) active: MBLT (n = 80), and 2) sham: deactivated negative ion generator (n = 40); each with identical engagement parameters (60-min duration; within 2-hrs of waking; daily over 28-day duration). Participant masking via deception balanced expectancy assumptions across arms. Outcome measures were assessed following a 14-day baseline (pre-intervention), following 28-days of device engagement (post-intervention), and 28-days after the post-intervention assessment (follow-up). Primary outcomes were sleep measures, including continuous wrist-based actigraphy, self-report, and daily sleep dairy entries. Secondary/exploratory outcomes included cognition, mood, quality of life, circadian rhythm via dim light melatonin onset, and biofluid-based biomarkers. Participant drop out occurred in <10% of those enrolled, incomplete/missing data was present in <15% of key outcome variables, and overall fidelity adherence to the intervention was >85%, collectively establishing feasibility and acceptability for MBLT in Veterans with mTBI.

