## Materials and methods

### Overview and ethics

LION is a sham-controlled, participant-masked, randomized controlled trial (NCT03968874), investigating primarily, the efficacy of morning bright light therapy (MBLT) to improve sleep quality, cognitive function, and quality of life in Veterans with mTBI, and secondarily, the feasibility and acceptability of implementing a fully remote clinical trial within the VA. Participants were randomized and allocated 2:1 to active (MBLT) or sham (negative ion generator) study arms, with a target total sample size of n = 120 participants with complete pre- and post-intervention data (~80% of the data has been collected so far). Primary outcomes were changes between groups from baseline to post-intervention (28 days), and baseline to follow-up (56 days). All participants that expressed interest, screened eligible, and were enrolled in the study were processed according to the Standard Protocol Items and Recommendations for Interventional Trials (SPIRIT) guidelines (Fig 1). This project is sponsored by the Military Traumatic Brain Injury Initiative (MTBI^2^) and approved by a joint Institutional Review Board (IRB) at the VA Portland Health Care System (VAPORHCS; #4268 and #4002) and Oregon Health & Science University (OHSU; #19411), as well as the Department of Defense Office of Human Research Oversight (OHRO). All participants provided, or will provide, verbal and written informed consent prior to participation.

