**Fig 1 pone.0305305.g001:**
[figure not shown]
SPIRT outcomes across time. The Standard Protocol Items: Recommendations for Interventional Trials (SPIRIT) timeline for LION.

The total target sample size of n = 120 participants is based on a priori power analyses considering mean insomnia severity index score as the primary outcome (see below). Using a two-sided students t-test design comparing MBLT to sham (pre- to post-intervention), the minimal detectable clinically relevant between-group difference was set at 7% with a standard deviation of 12% within MBLT and 7.3% within sham groups. This approach achieves β = 0.15 with α = 0.05 (i.e., 85% power; 15% probability of incorrectly accepting the null hypothesis) [49,50].

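### The powered test (ISI, pre to post, two-sided 0.05) is not the test the plan writes, so the level and power of the deciding comparison are undefined

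*Protocol article*

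**What the plan says.** **Powered test.** The sample-size paragraph (after Fig 1 in the protocol article) takes mean ISI as the primary outcome and describes the comparison as "Using a two-sided students t-test design comparing MBLT to sham (pre- to post-intervention". The difference is 7%, with SD 12% in MBLT and 7.3% in sham. It concludes: "This approach achieves β = 0.15 with α = 0.05 (i.e., 85% power; 15% probability of incorrectly accepting the null hypothesis".

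**Planned test.** Statistical analyses specifies a three-visit mixed model for each outcome: "The main effects in each model will be the treatment and time effects, including a treatment-by-time interaction effect". It continues: "With a significant omnibus test suggesting the global null hypothesis is rejected, a Bonferroni or Tukey HSD post-hoc analysis will be performed". The same section says: "The Benjamini-Hochberg procedure will be used to control the false discovery rate for primary outcomes". It does not name the effect that the omnibus test covers, choose between Bonferroni and Tukey, or count the comparisons or the primary outcomes.

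**Primary outcome.** The abstract says: "Primary outcomes were sleep measures, including continuous wrist-based actigraphy, self-report, and daily sleep dairy entries". Against that, the sample-size paragraph, the Primary subsection of Outcomes and the Results text after Fig 5 all treat ISI as primary. Table 3 lists ISI as the primary sleep outcome and puts actigraphy and diary under additional sleep outcomes.

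**Primary time.** Overview and ethics says: "Primary outcomes were changes between groups from baseline to post-intervention (28 days), and baseline to follow-up (56 days". The subsection on self-report, actigraphy and sleep diary says: "The primary comparison across timepoints was pre- vs post-intervention".

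**The concern.** A confirmatory trial needs one identifiable comparison, tested at a stated level, to which the power statement applies. Here that statement belongs to a single ungated t-test at 0.05. The analysis section offers no direct route to that comparison: every contrast sits behind an omnibus test and a further correction. Depending on the reading, the between-arm difference in ISI change could be tested at 0.05, at a fraction of 0.05, or only if another test is significant first.

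The competing statements of what is primary widen the choice, because the number of primary outcomes sets the Benjamini-Hochberg family. The abstract and the overview also cannot both hold: diary and actigraphy stopped before follow-up, so they have no day-56 value. Investigators know that every ion generator is inactive, so these choices should be closed in writing before outcome data are analysed.

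**Working it through.** **1. Reproduce the stated power.** Inputs from the sample-size paragraph and Introduction: difference 7; SD 12 (MBLT, n = 80) and 7.3 (sham, n = 40); two-sided 0.05.

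- SE = √(12²/80 + 7.3²/40) = √(1.800 + 1.332) = 1.770
- 7 / 1.770 = 3.955
- Power = Φ(3.955 − 1.960) = **97.7%** (Welch noncentral t: 97.5%)

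A pooled-SD Student test gives 91.9%. None of these is 85%. With the stated SDs, 85% power at 2:1 needs only 69 (normal) to 72 (Welch) participants.

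One variant does match. With SD 12 in both arms, SE = 12 × √(1/80 + 1/40) = 2.324, 7 / 2.324 = 3.012, and power = Φ(3.012 − 1.960) = **85.4%**; the required N is 40 + 80 = 120. That sets aside the stated sham SD.

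**2. Power at a Bonferroni-corrected level.** Power = Φ(7/SE − z), with z the two-sided critical value at 0.05/k. The article does not give k, so each k is an assumption.

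| k | z | SD 12 / 7.3 | SD 12 in both arms | N for 85% (SD 12 in both) |
|---|---|---|---|---|
| 1 | 1.960 | 97.7% | 85.4% | 120 |
| 2 | 2.241 | 95.7% | 78.0% | 144 |
| 3 | 2.394 | 94.1% | 73.2% | 156 |
| 15 | 2.935 | 84.6% | 53.1% | 210 |

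k = 15 is the number of pairs among six arm-by-visit means (6 × 5 / 2). The between-arm difference in change is not one of those pairs, so that row shows the cost of testing at 0.05/15, not the power of a test the plan names.

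The pooled Student test on the stated SDs lies between the columns. Pooled SD = √[(79 × 144 + 39 × 53.29)/118] = 10.68, so SE = 2.068 and noncentrality = 3.385. Noncentral-t power is 91.9%, 86.6%, 82.9% and 65.1% for k = 1, 2, 3 and 15.

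**3. Adding the gate.** The gate was simulated as a 2-df treatment-by-time test at 0.05 followed by the corrected pre-post contrast (20,000 runs, 80/40). Assumed: correlation 0.3 to 0.7 between the two changes, and a follow-up effect of 0, 3.5 or 7.

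| k | SD 12 / 7.3 | SD 12 in both arms |
|---|---|---|
| 2 | 93.8–95.4% | 73.8–76.8% |
| 3 | 92.9–93.6% | 71.2–72.3% |
| 15 | 82.0–83.0% | about 51% |

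**4. Type I error.** Rejecting the contrast requires passing the gate as well as the corrected test, so its error rate cannot exceed the level of the contrast itself. Simulated under the full null with the stated SDs: 2.5% (gate, no correction), 1.9% (k = 2), 1.5% (k = 3) and 0.3% (k = 15).

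**5. Baseline ISI.** With equal variances before and after and pre-post correlation ρ, the change score has variance proportional to 2(1 − ρ) and the baseline-adjusted score to 1 − ρ². The ratio is (1 + ρ)/2: 0.75 at ρ = 0.5 and 0.85 at ρ = 0.7, a reduction of 25% and 15%. The article gives no ρ.

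**The case against.** The body of the article largely ranks the outcomes already: ISI is called primary in several places, actigraphy and diary are called additional or supplemental, and pre versus post is named as the main comparison. If ISI is the sole primary outcome, Benjamini-Hochberg costs nothing. The treatment-by-time term carries the between-arm difference in change, and the omnibus test can be read as a test of that term. This is also a condensed article, and the exact contrast and family size are commonly left to a fuller plan.

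Much of this stands. The ranking makes the conflict easy to settle, and the missing comparison count is not itself a fault. But the abstract and overview still say something different. The gate and post-hoc step are stated rules, and the Introduction says the article presents the statistical analysis plan. Even if the omnibus test is the interaction, it covers two changes jointly for ISI and is not the single comparison that was powered.

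It is also fair that a mixed model with free baseline means is valid. Using baseline ISI is an improvement, not the repair of an error.

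**Conclusion.** The point holds as a mismatch between the powered test and the written one, together with a real conflict over primary outcome and time. The level and power of the deciding test are undefined, and 85% is not the power of the procedure as written.

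Three stronger inferences are tempting and not supported:

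- **That power falls well below 85%.** On the stated SDs with unequal variances, power stays at 94% or more for two or three comparisons and is 84.6% at fifteen. The figures of 78%, 73% and 53% require SD 12 in both arms, which the article does not state. A pooled analysis would leave a thinner margin. Every figure depends on an assumed k.
- **That alpha is inflated.** For this contrast, the gate and correction push the error rate below 5%.
- **That the primary contrast would never be tested, or that a common time effect opens the gate.** Both are possible readings of unspecific wording, not what the text says.

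A separate fault comes out of the check: 85% at 120 does not follow from the SDs printed beside it.

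**What to change.** 1. Name one primary test: ISI at post-intervention (day 28), MBLT versus sham, two-sided 0.05.
2. Estimate it as one pre-specified contrast from the mixed model with baseline means constrained equal across arms, or by ANCOVA on pre-intervention ISI.
3. Remove the omnibus gate and the Bonferroni/Tukey step for this contrast.
4. Move day-56 ISI, actigraphy, diary and the other sleep scales to a listed secondary family under Benjamini-Hochberg.
5. Align the abstract, Overview and ethics, and Statistical analyses with this.
6. Restate the power with the SDs actually used. If more than one primary test is kept, give their number and recompute power at the adjusted level.

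The cost is wording only. Results states that outcomes have not yet been explored, so the change can still be pre-specified. The downside is that day 56 and actigraphy lose the primary label, which the Outcomes section and Table 3 already imply.
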